## Abstract

**Background:**

Lung cancer stigma (i.e., perceived and internalized negative appraisal and devaluation associated with lung cancer) is a clinically significant psychosocial concern among individuals diagnosed with lung cancer. Stigma has been linked to increased psychological distress, higher depressive symptoms, anxiety, lower quality of life, and reduced engagement in care. However, few patient-centered interventions address lung cancer stigma. Mindful Self-Compassion (MSC) is a promising approach that promotes emotional resilience and reduces psychological distress. However, MSC has not been tailored for the needs of people with lung cancer. To address this gap, we developed Mindful Self-Compassion for Lung Cancer (MSC-LC)—a disease-specific adaptation designed to reduce stigma by cultivating self-compassion. This study aims to assess the feasibility, acceptability, and preliminary efficacy of MSC-LC among individuals with lung cancer who report elevated stigma.

**Methods:**

Theoretically grounded in the Conceptual Model of Lung Cancer Stigma, the Health Stigma and Discrimination Framework, and the CDC Map of Adaptation, this pilot trial uses a parallel-group randomized controlled design (1:1 allocation) comparing MSC-LC to an enhanced standard-of-care waitlist control group (CTL). We aim to enroll 60 adults diagnosed with lung cancer (*n*=30 per condition) who exceed a validated cutoff for elevated stigma on the Lung Cancer Stigma Inventory. MSC-LC includes weekly 90-min virtual group sessions co-facilitated by trained interventionists and home practice assignments between sessions. Feasibility and treatment fidelity (primary outcomes) will be assessed using quantitative benchmarks (e.g., recruitment, retention, session attendance, interventionist adherence). Acceptability will be evaluated through qualitative interviews. Secondary outcomes including stigma, self-compassion, depressive symptoms, anxiety, and spiritual well-being will be collected at baseline, mid-intervention, post-intervention, and longer-term follow-up. Quantitative and qualitative data will be integrated at the interpretation phase to examine signals of change and inform refinement and implementation.

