### Sample size justification

Consistent with methodological guidance that pilot trial sample size should be large enough to estimate key feasibility parameters with acceptable precision, minimum sample size was determined based on feasibility objectives and progression criteria rather than testing for intervention efficacy [38].

A priori progression criteria were defined for recruitment, retention, session attendance in the MSC-LC condition, and treatment fidelity. Recruitment will be considered feasible if at least 50% of eligible participants enroll and not feasible if recruitment uptake is 33% or less. Retention will be considered feasible if 75% or more of participants complete follow-up assessments and not feasible if retention is 50% or less. MSC-LC attendance will be considered feasible if at least 60% of participants attend six or more sessions and not feasible if 33% or fewer attend six or more sessions. Treatment fidelity will be considered feasible if at least 80% of intervention components are delivered per session and not feasible if delivery is 50% or less. Using the normal approximation method for a two-arm parallel design with one-sided *α* =.05 and 90% power to evaluate these feasibility thresholds [38], the *minimum* required sample size was *n* = 62 (*n* = 31 per condition).

MSC-LC will be delivered across three planned cohorts, each designed to include approximately 10–15 participants to facilitate meaningful discussion and interpersonal exchange [14, 39]. Accordingly, total recruitment may range from 62 to 90 participants to ensure adequate group size across cohorts. Although the sample size is consistent with accepted conventions for pilot trials, we acknowledge that it limits the precision and generalizability of the quantitative findings. The analyses are intended to inform the design and feasibility of a future fully powered trial.

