### Intervention description

#### Mindful Self-Compassion for Lung Cancer (MSC-LC)

MSC-LC is a group-based psychosocial intervention that consists of 10 consecutive weekly 90-min sessions, facilitated by two trained interventionists. The overall goal of the intervention is to enhance recognition and responsiveness to difficult thoughts and emotions (particularly those arising from their diagnosis of lung cancer and any associated stigma) and to build self-compassion skills that facilitate patients’ ability to turn inward to those thoughts and feelings with mindfulness, connectedness, and self-kindness. The treatment manual is adapted based on the Mindful Self-Compassion Teacher Guide from the Center for Mindful Self-Compassion [14, 39].

Each session follows an agenda with highly structured scripts covering self-compassion topics, which are carefully organized to build upon one another (Table 1). Specifically, the program begins with introductions and setting group expectations before sequentially building core MSC-LC skills focusing on mindfulness, kindness and compassion for others, kindness and compassion toward oneself, managing difficult emotions, responding to distress that arises from lung cancer stigma, navigating challenging relationships, and a final reflection and integration session. A silent retreat session midway through the intervention program offers an uninterrupted opportunity for intensive practice of core skills. Each session includes didactic or psychoeducational topics (e.g., “what is self-compassion?”), experiential activities, guided meditations, group discussion (both in the full group and within pairs or trios), and home practice assignments to reinforce learning. Sessions are delivered in small groups (typically 8–12 participants), and participants are asked to join virtually from a private space to support a confidential and supportive group environment. Sessions are co-facilitated by two trained interventionists to allow brief individualized support in a private breakout room for participants experiencing heightened distress, with follow-up contact from the study team and reminders of available support resources as needed.

**Table 1 Tab1:** Overview of sessions in Mindful Self-Compassion for Lung Cancer (MSC-LC)

Session	Psychoeducational/Didactic	Skills/Meditation	Home Practice

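### The abstract's enrolment target of 60 is below the stated minimum of 62, and the MSC-LC group size is given two ways that do not both lead to the stated maximum of 90

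*Protocol article*

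**What the plan says.** Three places in the protocol article bear on the planned size.

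- Abstract, Methods: "We aim to enroll 60 adults diagnosed with lung cancer", with 30 per condition.
- Sample size justification: "the *minimum* required sample size was *n* = 62 (*n* = 31 per condition". The same section says that "MSC-LC will be delivered across three planned cohorts, each designed to include approximately 10–15 participants", and that "total recruitment may range from 62 to 90 participants to ensure adequate group size across cohorts".
- Intervention description (MSC-LC): "Sessions are delivered in small groups (typically 8–12 participants".

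Allocation is 1:1, and attendance is assessed in the MSC-LC arm only. The sample size section derives its minimum from progression thresholds for feasibility, with a one-sided 5% level and 90% power.

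**The concern.** A recruitment target cannot sit below the trial's own minimum. Both figures are printed in the same article, so this is not a detail left to a fuller document. A reader who takes the abstract as the plan would consider the trial complete at 60, while a reader of the methods would count 60 as a shortfall.

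The group sizes raise a related problem. The number in the MSC-LC arm is the number of cohorts times the cohort size, and the two stated cohort sizes lead to different arms and different maximum totals. In a pilot whose primary outcomes are feasibility benchmarks, the target, minimum, maximum and group size should follow from one another.

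**Working it through.** **Inputs.** From the sample size section: one-sided α = 0.05, power 90%; attendance not feasible at 33%, feasible at 60%; retention not feasible at 50%, feasible at 75%; three cohorts of about 10–15. From the intervention description: groups of 8–12. From the randomization section: 1:1 allocation. The quantitative analyses section puts the upper retention threshold at 70%. I use 75% because that is the figure printed beside the calculation.

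**Step 1: reproduce the minimum.** One-sample normal approximation, with z(0.95) = 1.645 and z(0.90) = 1.282:

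n = [z(0.95)·√(p0(1−p0)) + z(0.90)·√(p1(1−p1))]² / (p1−p0)²

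- Retention, 50% vs 75%: [(1.645×0.500 + 1.282×0.433)/0.25]² = (1.377/0.25)² = 30.35, rounded up to 31.
- Attendance, 33% vs 60%: [(1.645×0.470 + 1.282×0.490)/0.27]² = (1.401/0.27)² = 26.9; with continuity correction 30.5, rounded up to 31.

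Either route gives 31, and 2 × 31 = 62. A two-sample comparison of the same proportions would need 63 (retention) or 57 (attendance) per arm, so it is not the source of 31. The plan's 62 therefore reproduces, and the abstract's 60 is the figure that does not fit.

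**Step 2: what the gap costs.** Power = Φ{[(p1−p0)·√n − 1.645·√(p0(1−p0))] / √(p1(1−p1))}:

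| n in one arm | Attendance 33% vs 60% | Criterion 50% vs 75%, one arm |
|---|---|---|
| 30 | 92.5% | 89.7% |
| 31 | 93.2% | 90.6% |

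For example, attendance at 30: (0.27×5.477 − 0.773)/0.490 = 1.44, and Φ(1.44) = 92.5%. The difference is under one percentage point in each column. Retention is defined over both arms, so its relevant n is the whole sample; the same formula then gives 99.5% at 60 and 99.6% at 62.

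**Step 3: cohort arithmetic.** Three cohorts, then doubled for 1:1 allocation:

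| Group size | MSC-LC arm | Total |
|---|---|---|
| 8–12 | 24–36 | 48–72 |
| 10–15 | 30–45 | 60–90 |

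- The maximum of 90 follows from the larger range (3 × 15 × 2 = 90). With 8–12 the maximum is 3 × 12 × 2 = 72.
- The minimum of 31 needs a mean of 31/3 = 10.3 per cohort. Three groups of 8, 9 or 10 give 24, 27 or 30, so the low end of 8–12 misses it, and the floor of 10–15 misses it by one.
- Groups of 11, 10 and 10 give 31 and lie inside both ranges. An arm of 31–36 (62–72 in total) satisfies both ranges and the minimum.

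**The case against.** The strongest reply is that this is editorial. The methods section carries the operative figure, that figure reproduces, and two participants change nothing of substance. On power, that stands.

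On group size, both ranges are hedged as approximate or typical, and they may describe different things: the number assigned to a cohort and the number present at a session. Absence is expected, since the retention section lets participants miss up to five sessions and stay in the group. It also happens that 80% of 10–15 is 8–12 (0.8×10 = 8, 0.8×15 = 12). The document does not state this link, so it remains an inference, but it means the two ranges may not be a true contradiction. It does not remove the need to say which is meant.

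Two stronger readings are tempting, and the text supports neither.

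- A reader might infer that the trial could run with three groups of 8 and lose real power. The sample size section rules out an arm of 24, because 48 in total is below its own minimum. Any loss computed for retention from one arm's size would also use the wrong denominator: over both arms, 48 participants give about 98% power for 50% vs 75%.
- A reader might infer that the open range of 62 to 90, with ongoing review of retention and adherence, lets recruitment close on the results. The section ties the range to filling the groups, the analysis section plans no interim analyses, and nothing links the review to the final size.

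**Conclusion.** The inconsistency is real and small. The abstract's 60 (30 per condition) is 2 below the stated minimum of 62 (31 per condition) and lies outside the 62–90 range. The group sizes of 8–12 and 10–15 do not both lead to the stated maximum: 8–12 stops at 72 in total, and its lower end falls short of 31 in MSC-LC. The two ranges are nevertheless compatible with the minimum, because 31–36 in MSC-LC meets both, so the design is not arithmetically impossible.

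The effect on power is negligible, less than one percentage point per criterion between 30 and 31. This rests on the one-sample normal approximation, which reproduces the plan's figure although the article does not print its formula, and on the 75% retention threshold from the sample size section.

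**What to change.** 1. In the abstract, replace the target of 60 (30 per condition) with a minimum of 62 (31 per condition) and the range of 62 to 90 from the sample size section.
2. Reconcile the group sizes in the sample size section and the intervention description so that the stated maximum follows: 72 with groups of at most 12, or 90 with groups of at most 15. Alternatively, if that is what is meant, keep both and state that 10–15 is the number assigned per cohort and 8–12 the expected attendance per session.

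The cost is wording in three places. No calculation, design element or analysis changes, unless the authors choose the smaller group size, in which case the upper recruitment limit changes with it.

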**Discussion:**

This study will address the gap of patient-centered interventions that target the reduction of lung cancer stigma. Findings will inform the rigorous evaluation of the efficacy of MSC-LC to reduce stigma among individuals with lung cancer.

**Trial registration:**

The protocol for this study has been registered on ClinicalTrials.gov (ID: NCT06191939). First posted December 20, 2023, last update posted July 17, 2025. https://clinicaltrials.gov/study/NCT06191939.

## Background

Adults diagnosed with lung cancer frequently report experiences of stigma (i.e., perceived and internalized negative appraisal and devaluation associated with lung cancer), a critical psychosocial issue that contributes to greater distress, higher depressive symptoms, higher anxiety, worse quality of life, greater sleep disruption, and more bothersome physical symptoms [1–7]. Importantly, lung cancer stigma often carries a moral dimension, rooted in perceptions of personal responsibility or blame (e.g., attribution theory) [8], which can intensify distress and further marginalize people diagnosed with lung cancer [9]. Reduction of stigma for this vulnerable and growing patient population is an urgent need [10, 11]. Despite these associations, there is a gap in the field regarding empirically supported, patient-focused interventions that target the reduction of lung cancer stigma [12, 13].

To address this need, we developed Mindful Self-Compassion for Lung Cancer (MSC-LC)—a disease-tailored, mindfulness-based psychosocial intervention that aims to reduce lung cancer stigma by cultivating self-compassion skills [14]. MSC-LC was developed through a rigorous, multi-phase adaptation process to enhance relevance, accessibility, and safety for individuals with lung cancer [14]. The intervention builds upon the empirically supported Mindful Self-Compassion (MSC) program, an 8-week, group-based program that has demonstrated efficacy in increasing self-compassion and reducing shame, self-criticism, anxiety, and depression in non-cancer populations [15–20].

Self-compassion is defined as directed kindness towards oneself in times of suffering [21], and it is increasingly recognized as a protective psychosocial factor in the context of chronic illness [18, 19]. Among adults with lung cancer, higher levels of self-compassion have been shown to buffer the association between stigma and depression [22], suggesting it may serve as an effective psychological target for intervention. However, given several anticipated challenges associated with standard delivery of MSC to lung cancer patients (e.g., breathing challenges that arise during breath-focused meditations, fatigue that interferes with attending 3-hour sessions), the investigators created MSC-LC to better meet the needs of people living with lung cancer [14, 23–25]. Informed by perspectives from individuals with lung cancer, psycho-oncology clinicians, expert MSC teachers, and stigma researchers, major adaptations include a shorter session length, modified breath- and movement-focused practices, simplified home exercises, and explicit inclusion of content that acknowledges, explores, and responds to the experience of lung cancer stigma [14].

Despite the plausibility of self-compassion as an intervention target and the rigorous adaptation process of developing MSC-LC, no randomized controlled trials (RCTs) to date have tested the feasibility of a group-based psychosocial intervention designed to reduce lung cancer stigma. As such, it is not yet known whether MSC-LC is acceptable to individuals diagnosed with lung cancer, feasible to deliver, and associated with meaningful reductions in stigma and related distress.

### Aims of the current study

The primary aim of this pilot RCT is to evaluate the intervention feasibility and treatment fidelity and acceptability of the MSC-LC program in adults with lung cancer who report clinically elevated stigma. The target for trial feasibility is 50% of eligible participants agreeing to enroll in the study and be randomized (recruitment), 30% attrition or lower (retention), and 60% of participants in the MSC-LC condition attending six or more session (attendance). The target for treatment fidelity is >80% of intervention components deliver per session (interventionist adherence to protocol) and average intervention delivery competency ratings greater than or equal to 4 out of 6 (indicating “competent” delivery) using a standardized assessment. Acceptability will be evaluated through qualitative feedback on appropriateness and satisfaction of the MSC-LC intervention.

This pilot trial will also explore whether MSC-LC is associated with improvements in lung cancer stigma, self-compassion, depressive symptoms, anxiety, and spiritual well-being (secondary outcomes), and examine theory-driven mechanisms of change. In addition, we will conduct post-intervention qualitative interviews with participants to identify salient experiences, mechanisms of change, and areas for refinement not captured in quantitative outcomes.

## Methods

### Study design

Theoretically grounded in the Conceptual Model of Lung Cancer Stigma, the Health Stigma and Discrimination Framework, and the CDC Map of Adaptation [26–28], the current study is a pilot, mixed-methods, parallel group RCT where participants are randomized with a 1:1 ratio to either the MSC-LC intervention (a 10-week, virtually-delivered, group-based psychosocial intervention focused on the development of mindfulness and self-compassion skills) or to an enhanced standard-of-care waitlist control group (CTL). The reporting of this protocol is aligned with the Standard Protocol Items Recommendations for Interventional Trials (SPIRIT) guidelines [29]. All procedures were approved by the Institutional Review Board (IRB) at Loyola Marymount University. Any protocol amendments will be submitted and approved by the IRB prior to making any changes to the study procedures.

### Participant eligibility

Inclusion criteria for participant eligibility include (1) being at least 18 years of age; (2) having a confirmed diagnosis of lung cancer, as per self-report and verified by treating clinician or medical record; (3) a score of 38 or higher (above the validated cutoff for clinically significant stigma burden) on the Lung Cancer Stigma Inventory (LCSI) [1, 30]; and (4) ability to read and respond to questions in English. Exclusion criteria include (1) inability to understand study procedures or the informed consent process, or observable interpersonal behaviors documented during screening (e.g., hostility or antagonism, violations of interpersonal boundaries) that would interfere with safe and constructive participation in a group-based intervention, as determined by the study clinician (Principal Investigator) in consultation with the screening research team member; (2) completed a course of Mindful Self-Compassion or an equivalent meditation training in the prior 12 months; and (3) use of antidepressant, anxiolytic, antipsychotic, or mood stabilizing medication(s) for which the dose has been initiated or changed within the 8 weeks prior to study entry. To accommodate the complex and individualized needs of people with lung cancer, participants will be permitted to continue their usual medical and psychological care during their study participation. The only restrictions are concurrent or recent (within the past 12 months) enrollment in another course focused on mindful self-compassion or similar mindfulness-based training (e.g., Mindfulness-Based Stress Reduction).

### Participant recruitment, screening, informed consent, and randomization

Our national recruitment approach will engage multiple strategies, including sharing study information with clinics, lung cancer survivorship groups, and non-profit organizations across the USA; direct messaging (via email and text) to existing registries of people who are interested in participating in clinical trials (e.g., ClinicalConnection); and direct-to-participant recruitment via social media and other web-based platforms [31–33]. We will contract with a third-party vendor (BuildClinical, LLC) to assist with direct-to-participant recruitment [34, 35]. BuildClinical deploys study-specific advertisements to engage participants on various social media and other digital platforms (e.g., Facebook, Google, WebMD). When individuals click the advertisement (e.g., “Join a Remote Study to Improve Lung Cancer Care”), they will be redirected to a study-specific landing page with study procedures, risks, benefits, and compensation. On the landing page, individuals are invited to complete a pre-screening questionnaire online (assessing age, diagnosis of lung cancer, and comfort responding to questions in English).

Interested and potentially eligible participants provide authorization to BuildClinical to provide their name and contact information to the study team. Potential participants recruited via other methods (e.g., outreach from a local non-profit organization) will be directed to a similar web-based form to complete a pre-screening questionnaire and provide their contact information. Then, the study team will contact potential participants via phone to complete a screening survey (verifying pre-screening responses and assessing study inclusion and exclusion criteria). All participants will be assigned a study participant ID at the onset of screening (prior to randomization), which will be used to facilitate questionnaire completion and de-identified data management. An overview of participant flow from initial contact through study completion is presented in Fig. 1.

**Fig. 1 Fig1:**
[figure not shown]
Schedule of enrollment, treatment, and data collection

Individuals confirmed as interested and eligible will then complete and digitally sign a HIPAA authorization for the release of protected health information, which authorizes the individual’s oncology care clinician to confirm the individual’s lung cancer diagnosis to the study team. The study team will confirm the participant’s diagnosis by reviewing a medical record note, which can be shared by the oncology care clinician via fax, mail, secure digital message or from by participant via self-uploading a file to a secure web-based form. All medical record notes will be destroyed promptly after confirming the participant’s diagnosis.

After confirming the participant’s diagnosis, the study team will contact the participant via secure teleconferencing software (e.g., Zoom) to maintain participant protections. To verify the participant’s identity, participants will be asked to present photo identification to the study team member for visual verification (no record of the photo identification will be retained by the study team). The study team member will verbally explain the study procedures, risks, benefits, compensation, and all information in the informed consent form. All participants will provide signed informed consent (digitally). All participants are provided with information for 24-h crisis support services (e.g., 988) at study onboarding and reminded of these resources as needed. Throughout the study, participants who experience psychological distress may contact the on-call study clinician (Principal Investigator) during working hours.

After providing signed informed consent, participants will be randomized to either the MSC-LC or CTL condition. Prior to randomization, a randomized allocation sequence will be generated using the NCI Clinical Trial Randomization Tool [36]. Parameters for generating the allocation sequence include an asymptotic maximal randomization method, a maximum tolerated imbalance of 2, and an allocation ratio of 1:1 without stratification. Randomization will not be stratified in this pilot study, informed by formative qualitative findings indicating participant preference for heterogeneous group composition and expert guidance emphasizing the importance of shared emotional experiences across varying clinical contexts (e.g., disease stage, treatment) within the MSC-LC intervention [14]. To prevent selection bias, the research staff is provided with a participant’s allocation only after that participant has provided informed consent and has been accepted into the trial. Because the MSC-LC intervention is delivered in group format, randomization occurs prior to baseline assessment to allow for scheduling alignment among those assigned to the intervention group. Due to the nature of the behavioral intervention, participants and interventionists cannot be blinded to condition assignment.

